# Endoscopic intraventricular hematoma evacuation surgery versus external ventricular drainage for the treatment of patients with moderate to severe intraventricular hemorrhage: a multicenter, randomized, controlled trial

**DOI:** 10.1186/s13063-020-04560-3

**Published:** 2020-07-13

**Keywords:** Endoscopic surgery, External ventricular drainage, Intraventricular hemorrhage

## Abstract

**Background:**

The application of neuroendoscopy in intraventricular hemorrhage (IVH) has attracted more and more attention in recent years. Studies have shown that the use of neuroendoscopy for IVH evacuation has advantages over external ventricular drainage (EVD) alone. However, the cases of most current research are small and all of them are retrospective studies. The aim of this study is to explore the prognosis of patients with moderate to severe IVH who undergo endoscopic IVH evacuation surgery versus those who undergo EVD alone.

**Methods:**

The study is a prospective, randomized, controlled, multi-center clinical trial. Nine hundred and fifty-six subjects with moderate to severe IVH across four tertiary hospitals in China will be randomly assigned (1:1) to receive either endoscopic IVH evacuation surgery or EVD. The primary objective is to compare patients’ survival rate at 12 months after surgery.

**Discussion:**

The trial is designed to investigate the prognostic benefits of endoscopic IVH evacuation surgery for patients with moderate to severe IVH. Currently, it has never been investigated in a prospective randomized controlled clinical trial.

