## Methods

### Aim and objectives

Due to the insufficient evidence of endoscopic treatment for moderate to severe IVH, the aim of the study is to testify the efficacy of endoscopic IVH evacuation surgery compared with EVD.

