#### EVD group

The patient in the EVD group will be placed in the supine position and under general anesthesia. Bilateral external ventricular drainage will be performed regularly and unilateral drainage will be performed only when the other lateral ventricular has little hematoma and the circulation of cerebrospinal fluid is unobstructed. Surgeons usually select the point 1–2 cm before the coronal suture of the bleeding side and 2–3 cm next to the midline as the puncture point and puncture inwardly along the plane of the puncture point and the line of the ear. The surgeons will use a soft catheter with a guide needle to puncture in depth of about 5 cm and then pull out the guide needle. The next step is to fix the drainage catheter and suture the scalp incision. Postoperative CT will be done immediately to confirm the positioning of the soft catheter and stability of the hematoma. After at least 6 h postoperatively, we will administer 20,000 U urokinase with 5 ml saline every 8 h, and the catheter will be clamped for 1 h to allow drug–clot interaction and then reopened to allow for gravitational drainage. Subsequent CT scans will be done for any safety concern or every 24 h. Administration of urokinase will be stopped when the CT scans show that the circulation of cerebrospinal fluid is unobstructed. When CT scans show that the intracerebral hematoma is significantly reduced and the circulation of cerebrospinal fluid is unobstructed, the catheter shall be clamped for 24 h before removing the catheter. If there is no acute intracranial pressure increase, the catheter can be removed then.

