### Sample size

The sample size calculation results in a requirement of 956 patients. For EVD, the mortality rate is 23% in a meta-analysis of 4 randomized and 8 observational studies of patients with IVH [11]. In the CLEAR III trial, the mortality rate of the IVH patients treated with EVD plus rtPA is 18% at 180 days [13]. And the reported mortality rate of IVH patients treated with endoscopic surgery at 1 year ranges from 10 to 30% [1, 19, 20]. Based on previous studies and our own experience, we assume a 1-year overall survival rate of 70% (mortality rate of 30%) in both the reference group and the new surgical group. We plan for the trial to show non-inferiority of a new surgical method to the conventional method with a hazard ratio (HR) margin of 1.3 [21, 22]. The principle of the sample size calculation of a non-inferiority trial is different from that of a superiority trial where you want to demonstrate that one treatment or intervention is better than another. In the context of non-inferiority trials, the non-inferiority limit is used to calculate the sample size. The percentage for those on the experimental treatment is no worse than the percentage for those on the control treatment by the non-inferiority limit. In our study, the non-inferiority limit of the hazards ratio (HR) is set to 1.3. Accounting for a potential dropout rate of 5%, 956 patients (478 in each group) are needed to be enrolled, which ensured a power of 80%.

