### Statistical analysis

All statistical analyses in the study will be carried out by an analyst who is blinded as to the allocated intervention. The primary efficacy will be compared by an intention-to-treat analysis including all randomized patients.

Regarding the primary outcome (the 12-month survival rate), the Cox regression model method will be used to calculate the hazards ratio and the 95% confidence interval (CI). The non-inferiority of the new surgical method and the conventional method is determined according to whether the upper limit of the 95% CI of the HR is less than 1.3. If the upper limit of the 95% CI is less than 1.3, the non-inferiority is accepted. Otherwise, a non-inferiority conclusion cannot be reached.

For the secondary outcomes, the OS curves will be estimated using the Kaplan–Meier method. Continuous variables will be assessed for normality and equality of variances between groups. Discrete variables will be summarized by frequencies/proportions. For continuous variables, analysis of variance and/or regression will be used, where appropriate (hospital length of stay, hospitalization expenses). The comparison of the two groups with respect to frequencies/proportions will be performed using the *χ*^2^ test and, if necessary, Fisher’s test (proportion of patients who need ventricular-peritoneal shunt after surgery, incidence of postoperative hydrocephalus, postoperative intracranial infection rate). The ranked data of the two groups will be compared using the Wilcoxon rank-sum test (mRS).

At the annual monitoring meeting of the Data and Safety Monitoring Board, the treatment effectiveness (the 12-month survival rate) will be compared between the two groups. If one group has significantly more hazards than the other one (upper limit of the 95% CI of the hazards ratio is more than 1.3), the trial will be terminated.

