## Discussion

This study is a randomized controlled trial designed for patients with moderate to severe IVH. It aims to compare a relatively new surgical procedure (endoscopic IVH evacuation surgery) with the standard treatment (EVD). As with all surgical clinical trials, timing of the trial is crucial. If the trial is conducted too early, the new technique may still undergo too many modifications to allow application of a standardized procedure. In addition, recruitment might be too slow and the trial might turn out to be unfeasible. In contrast, if the trial is left too late, the new technique may become part of the mainstream treatment without adequate proof of its equivalence. In that case, too many patients might refuse randomization and the trial could also become unfeasible. Currently, the interest among endoscopy is strong and investigators are eager to enroll patients.

In summary, the available evidence suggests that endoscopic IVH evacuation surgery may be a valid alternative surgery to EVD with equal OS for patients diagnosed with moderate to severe IVH. This trial is aimed to provide high-quality evidence to support this hypothesis.

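### The abstract and aim speak of benefit and efficacy, but the only primary efficacy rule is non-inferiority at HR 1.3, with no pre-specified conclusion if the upper limit is also below 1.0

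*Protocol article*

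**What the plan says.** The purpose is worded differently in different places of the protocol article:

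- Abstract, Discussion paragraph: "The trial is designed to investigate the prognostic benefits of endoscopic IVH evacuation surgery for patients with moderate to severe IVH".
- Abstract, Methods paragraph: "The primary objective is to compare patients’ survival rate at 12 months after surgery". This is neutral.
- Methods, Aim and objectives: "the aim of the study is to testify the efficacy of endoscopic IVH evacuation surgery compared with EVD".
- Discussion: endoscopic surgery "may be a valid alternative surgery to EVD with equal OS for patients diagnosed with moderate to severe IVH".

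The hypothesis is named only later. Sample size plans to show "non-inferiority of a new surgical method to the conventional method with a hazard ratio (HR) margin of 1.3", with 30% one-year mortality assumed in both arms. Statistical analysis fits a Cox model in all randomised patients and accepts non-inferiority if the upper limit of the 95% confidence interval (CI) is below 1.3. It then adds: "Otherwise, a non-inferiority conclusion cannot be reached". No conclusion is attached to an upper limit below 1.0. The only other rule on the HR is the annual monitoring rule in the same section.

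On the comparator, the abstract's Background paragraph compares endoscopic patients "versus those who undergo EVD alone". The EVD group section states that "we will administer 20,000 U urokinase with 5 ml saline every 8 h".

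**The concern.** A reader of the abstract and aim would not learn that this is a non-inferiority trial. That reader could take a positive result as evidence of better survival, when the rule asks only whether the hazard of death is less than 30% higher. Conversely, if endoscopic surgery did lower mortality clearly, the plan as published has no step under which that would be the trial's formal conclusion. The interval would show it, but a superiority claim first written down after the data are seen would be open to the charge of being post hoc.

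The comparator wording adds to this, because a non-inferiority result means little unless the active control is identified. The Background first discusses EVD alone as drainage without a thrombolytic, so the same expression in the abstract can be read that way, although the EVD group receives urokinase.

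**Working it through.** **Inputs.** From Sample size: margin HR 1.3, 30% one-year mortality in both arms, 956 patients, 5% dropout, 80% power. From Statistical analysis: 95% CI, read here as two-sided. From Background and Sample size: endoscopic mortality of 10 to 30% at one year. Also from Sample size: mortality of 23% for EVD in a meta-analysis, and 18% at 180 days for EVD plus rtPA.

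**The plan's own figure.** The stated 956 does not follow from these inputs with 12 months of follow-up. Schoenfeld's formula gives deaths = 4(1.96 + 0.842)² / (ln 1.3)² ≈ 456.1, rounded up to 457. Then 457 / 0.30 gives 1,524 patients, and 1,524 / 0.95 gives 1,605. That is a separate matter. The present point does not depend on it, and the figures below take the planned size as given: 956 × 0.95 ≈ 908 evaluable.

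**What the margin allows.** Under proportional hazards, mortality at the margin is 1 − 0.7^1.3 = 37.1%, against 30%.

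**What result satisfies each step.** At 30% mortality, 908 × 0.30 ≈ 272 deaths. The standard error of ln HR is 2/√272 = 0.121.

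- Non-inferiority needs an observed HR below 1.3 × exp(−1.96 × 0.121) ≈ 1.02.
- Superiority needs an observed HR below exp(−1.96 × 0.121) ≈ 0.79.

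An observed HR between about 0.79 and 1.02 would therefore meet the published rule without showing a survival benefit.

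**Error rate of an added step.** An upper limit below 1.0 is necessarily below 1.3. The two null hypotheses (HR ≥ 1.3 and HR ≥ 1.0) are nested, and testing them in that order on one interval keeps the one-sided error at 0.025. The sample size for non-inferiority is unchanged.

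**Power of an added step.** HR = ln(1 − endoscopic mortality) / ln(1 − EVD mortality). Deaths = 908 × mean mortality. Power = Φ(|ln HR| × √deaths / 2 − 1.96).

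| Endoscopic vs EVD mortality | HR | Deaths | Power |
|---|---|---|---|
| 20% vs 30% | 0.626 | 227 | 94% |
| 22% vs 30% | 0.697 | 236 | 79% |
| 25% vs 30% | 0.807 | 250 | 40% |
| 20% vs 23% | 0.85 | 195 | 20% |

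If survival is truly equal, as the plan assumes, superiority would be declared only at the 2.5% error rate.

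**The case against.** The case against is substantial, and most of it stands.

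- *The plan does not promise to show benefit.* The abstract says investigate, its primary objective is a neutral comparison, and the Discussion's hypothesis of equal overall survival fits a non-inferiority design. A reader might infer that the trial sets out to prove superiority and tests something else. The text does not go that far.
- *Benefit may refer to other outcomes.* Background calls endoscopic mortality almost equivalent to that of EVD and places the reported advantages in hydrocephalus and shunt dependency. Statistical analysis compares these, infection and the modified Rankin score with ordinary difference tests. Non-inferior survival with gains elsewhere is a coherent reading, although the abstract does not limit the word in that way and the primary outcome is survival.
- *The trial could still reveal a survival benefit.* A reader might infer that the plan cannot conclude benefit even if survival is clearly better. That is too strong. The HR and its 95% CI will be reported, and a limit below 1.0 would be visible. What is absent is the pre-specified conclusion.
- *The comparator is defined in the body.* Background states that EVD, from that point on, means EVD with thrombolytic agents. A reader might infer that the comparator is misnamed throughout, but the aim, design and analysis all come after that definition. Only the abstract is ambiguous.
- *A superiority step is optional* and may stand in the full protocol or analysis plan, which are not shown. Its absence from the article is therefore not an error. Adding it is an improvement without cost.
- *Power scenarios can flatter the proposal.* Pairing 30% EVD mortality with low endoscopic mortality does so, which is why the 20% vs 23% row is included.

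What the objection does not remove is that the aims and the tested hypothesis are worded inconsistently within this one document.

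**Conclusion.** The point holds in limited form. The abstract and aim do not name the hypothesis that the trial tests, and the published rule attaches no conclusion to an upper limit below 1.0. Meeting that rule would be compatible with mortality up to about 37.1% against 30%, so it would not by itself support a survival benefit. The consequence lies in what may formally be concluded and how the result is described. The non-inferiority analysis itself is not invalid on this account.

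The figures assume proportional hazards, a two-sided 95% interval, 908 patients contributing full information, and superiority judged once, at the final analysis. Power for superiority is modest in several plausible scenarios, so the step should not be presented as a powered aim.

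**What to change.** 1. Name non-inferiority on 12-month survival, with the HR margin of 1.3, in the abstract and in Aim and objectives.
2. Reconcile the comparator wording in the abstract with the definition in Background and with the EVD group section, both of which include a thrombolytic.
3. Pre-specify a fixed sequence on the same intention-to-treat Cox model. If the upper 95% limit is below 1.3, conclude non-inferiority. If it is also below 1.0, conclude superiority. State that no survival benefit is claimed from the first step alone.
4. Say that the second step is not the basis of the sample size.

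If the sponsor does not want the second step, the alternative is to stop using the language of benefit for survival. The cost is wording only, with the same model and interval, no extra alpha and no extra patients. The change should be made before any outcome comparison by arm is seen by those who would write it.

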**Trial registration:**

ClinicalTrials.gov, NCT04037267. Registered on 26 July 2019.

## Background

Spontaneous intraventricular hemorrhage (IVH) is defined as eruption of blood into the cerebral ventricular system caused by rupture of brain arteries, veins, and capillaries instead of trauma. The mortality rate of IVH varies from 50 to 80% in the absence of specific treatment [1].

Primary IVH is confined to the ventricles while most IVH is secondary to intracranial hemorrhages (ICH) involving the thalamus and basal ganglia [2]. IVH is an independent predictor for poor outcome of patients with ICH [3]. According to the results of the STICH trial [4–6], the prognosis of patients with IVH is worse than that of patients without IVH (*p* < 0.00001) and if IVH is associated with hydrocephalus, the prognosis will be the worst.

Although external ventricular drainage (EVD) without thrombolytic agents is firstly used to help drain blood from the ventricles, using EVD alone may not effectively improve the patients’ outcome because of the slow rate of removing intraventricular blood [7]. With increasing clinical studies reporting that intraventricular administration of thrombolytic agents may reduce mortality by accelerating clot lysis [8–10], there has been more interest in using thrombolytic agents as adjuncts to EVD in the setting of IVH. A meta-analysis of 8 observational and 4 randomized studies of patients with IVH treated with EVD (*n* = 149) or EVD with fibrinolysis (*n* = 167) found a significant decrease in mortality from 47 to 23% (OR, 0.32; 95% CI, 0.19–0.52) [11]. Thus, in 2015 AHA/ASA spontaneous cerebral hemorrhage diagnosis and treatment guidelines [12], EVD plus recombinant tissue-type plasminogen activator (rtPA) in IVH patients is suggested, which has a fairly low complication rate; however, the efficacy and safety of this treatment are uncertain (Class IIb; Level of Evidence B).

In 2017, the phase 3 randomized CLEAR III trial, which is the largest trial to test whether using alteplase in removing intraventricular hemorrhage improves functional outcome compared with the placebo (saline), showed that the primary outcome (good functional outcome defined as a modified Rankin Scale score of 3 or less at 180 days) was similar in two groups (alteplase group 48% vs control group 45%; RR, 1.06 [95% CI, 0.88–1.28; *p* = 0.554]) [13]. Although the CLEAR III trial failed to reveal the superiority of thrombolytic agents in its primary outcome, the treatment group had a lower mortality rate (alteplase 46 [18%] vs saline 73 [29%], *p* = 0·006), which is a favorable evidence for making clinical decisions [13].

Several drawbacks of EVD with using thrombolytic agents (mentioned as EVD below) are also found in clinical practice, and the major one is that the catheters need to be removed or replaced regularly which increases the risk of infection.

Alternative procedures have also been reported recently and the endoscopic surgery appears to be the most promising treatment [1, 14–20]. Compared with the microscopic surgery, the endoscopic surgery provides better illustration and close-up view of the operative field, which makes the surgery safer and reduces surgical trauma to the patients.

The mortality rate of IVH patients treated with endoscopic surgery at 1 year ranges from 10 to 30%, which is almost equivalent to the efficacy of EVD [1, 19, 20]. Several studies have shown that endoscopic surgery for IVH evacuation (with EVD) has advantages over EVD alone [1, 18], which revealed that the incidence of postoperative hydrocephalus and the dependency for ventricular-peritoneal shunt surgery postoperatively is lower in endoscopic group. The following factors might also be of great importance for improving patients’ outcome: (1) the endoscopic surgery could remove hematoma and improve cerebral perfusion quickly, reducing extrusion effects on critical cerebral structures and neurotoxic effects of the hematoma decomposition products; (2) neurosurgeons could evacuate the hematoma under direct vision, which increases the hematoma clearance rate and reduces the probability of postoperative rebleeding; and (3) the drainage catheter could be placed under direct view, improving placement accuracy and avoiding damage to the choroid plexus. However, the cases of most current research are small and all of them are retrospective studies. There are also no such clinical trials registered, which means there is no high-level evidence to verify the effect of endoscopic treatment for IVH because of the small sample size and retrospective analysis of the reported studies.

Based on this, we intend to conduct a randomized, controlled, multi-center clinical trial to compare the prognosis of patients who undergo endoscopic IVH evacuation surgery versus those who undergo external ventricular drainage for moderate to severe IVH.

## Methods

### Aim and objectives

Due to the insufficient evidence of endoscopic treatment for moderate to severe IVH, the aim of the study is to testify the efficacy of endoscopic IVH evacuation surgery compared with EVD.

### Study design

The study is a prospective, multicenter, randomized, controlled trial. A flowchart is shown in Fig. 1. Patients with IVH will be randomly assigned (1:1) to the endoscopic group and the EVD group.

**Fig. 1 Fig1:**
[figure not shown]
A flowchart of the study design

The Standard Protocol Items: Recommendations for Interventional Trials (SPIRIT) checklist is provided in Additional file 1.

### Setting

The study will be performed at 4 neurosurgical centers in China (Jinling Hospital, Inner Mongolia People’s Hospital, The First Affiliated Hospital of Lanzhou University, and Shengjing Hospital Affiliated of China Medical University). The organizer has set up an expert panel to ensure that each center has the proper surgical technique.

First, the center applying to participate in the study needs to provide at least two videos of unedited endoscopic IVH evacuation surgery and EVD, respectively, and provide clinical information of at least 5 cases performed with endoscopic IVH evacuation surgery and EVD (including preoperative imaging data, surgical records, and postoperative imaging data). The expert panel will judge whether the applicant has the qualification to participate in the study based on the above information.

### Inclusion and exclusion criteria

#### Inclusion criteria

Patients of either sex, 18–70 years of age.Clinical manifestation as moderate to severe IVH, such as severe headache, hemiplegia, aphasia, or unconsciousness.Disease onset within 24 h.Graeb scale > 4.Glasgow Coma Scale < 13.CT scan showing the existence of hemorrhage breaking into the ventricles or primary intraventricular hemorrhage, and the bleeding volume being larger than 50% of the volume of the lateral ventricle.

#### Exclusion criteria

Age < 18 years or > 70 years.Patients with a history of severe cardiopulmonary dysfunction (NYHA level III or IV), chronic kidney disease (GFR < 60 ml/(min*1.73m^2^)), blood disorders (anemia (Hb < 90 g), hemophilia, myelodysplastic syndromes), cancer.Patients who have any severe pre-existing physical or mental disabilities or comorbidities (palsy, dementia) that will interfere with the assessment of the outcome.CT scan showing the existence of cerebellar hemorrhage or brain stem hemorrhage.Cerebrovascular diseases detected by CTA/MRA/MRV/DSA examinations (choosing 1 or 2 examinations), such as aneurysm and cerebrovascular malformation.CT scan suggesting the presence of brain tumors.Patients with a history of coagulopathy or long-term use of anticoagulants.

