### Randomization

We adopt a central randomization method based on the mobile client randomization tool “Randomization Allocation Tool” (RAT) to achieve random assignment of patients into two groups at a 1:1 ratio. If the subject is qualified for the trial and signs the informed consent form, the investigator authorized by each center can input the relevant information (e.g., age, gender, the bleeding volume, scores of Graeb scale, and GCS) of the corresponding subject in the mobile phone client. After the administrator approves the confirmation, the assigned group is immediately fed back to the researcher’s mobile phone, and the researcher will perform the prescribed surgical treatment according to the specified group. Possible facts that may impact the outcomes of the patients, such as age, gender, scores of Graeb scale, and GCS, will be considered by a minimization random allocation system.

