### Treatment

#### Endoscopic group

The patient in the endoscopic group will be placed in the supine position and under general anesthesia. Endoscopy is performed using a rigid endoscope (Karl Storz, German). The side with more hemorrhage will be taken as the surgical side and a transverse incision of about 3 cm in length will be performed 1–2 cm in front of the coronal suture, 2–3 cm beside the midline. Then, a bone window with a diameter of 2–3 cm will be made and we will cross-incise the dura mater. Next, the surgeons insert the endoport (Vycor Medical, USA) into the lateral ventricle, which will become the endoscopic work channel. The hematoma will be removed by a technique using irrigation and aspiration. After exposing the choroid plexus of the lateral ventricle, surgeons should strive to clear the hematoma in the third ventricle through the interventricular orifice. At the same time, the blood clots will be removed with grasping forceps and if there is bleeding, bipolar coagulation can be used to stop bleeding. During the operation, the veins, choroid plexus, and ventricular wall should be carefully protected and blood clots that are closely adhering to the choroid plexus are not required to be completely removed. The third ventriculostomy and pellucid septostomy should be performed if possible. The ventricular drainage catheter will be placed on the surgical side. The dura and skin will be closed in a routine manner. An immediate postoperative CT scan will be performed to assess the residual hematoma. After 6 h postoperatively, we will administer 20,000 U urokinase with 5 ml saline every 8 h through the catheter, and the catheter will be clamped for 1 h to allow drug–clot interaction and then reopened to allow for gravitational drainage. Subsequent CT scans will be done for any safety concern or every 24 h. Administration of urokinase will be stopped when the CT scans show that the circulation of cerebrospinal fluid is unobstructed. When CT scans show that the intracerebral hematoma is significantly reduced and the circulation of cerebrospinal fluid is unobstructed, the catheter shall be clamped for 24 h before removing the catheter. If there is no acute intracranial pressure increase, the catheter can be removed then.

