### Outcome measures

The primary outcome is the survival rate of patients at 12 months after surgery.

In addition, secondary outcome measures include treatment-related morbidity, as evaluated by the following items:
Overall survival (time to death after surgery).Modified Rankin score (preoperational, 1 month, 3 months, 6 months, 12 months).Proportion of patients who need ventricular-peritoneal shunt after surgery (1 month, 3 months, 6 months, 12 months).Incidence of postoperative hydrocephalus (1 month, 3 months, 6 months, 12 months).Postoperative intracranial infection rate (1 month, 3 months, 6 months, 12 months).Hospital length of stay.Hospitalization expenses (costs spent during treatment for IVH in hospital).

The relevant data will be collected by two data entry staff independently.

The study will include a follow-up period of 12 months. Patients will stay in the hospital for at least 2 weeks postoperatively to complete the required assessments (e.g., GSC and Graeb scale, blood and urine tests, brain CT and MRI, CTA/MRA/MRV/DSA) which are shown in Table 1. The final study follow-up is scheduled at 12 months after surgery. The patients will be reminded to return to the hospital by phone calls at 1 month, 3 months, 6 months, and 12 months after surgery to perform associated clinical examinations and tests (e.g., blood and urine tests, brain CT and MRI, modified Rankin Scale, records of the complications and survival state).

**Table 1 Tab1:** Enrollment and assessments in the trial

Item	Screening period	Follow-up							
		Operation day	1 day after the operation	7 days after the operation	2 weeks after the operation	1 month after the operation	3 months after the operation	6 months after the operation	12 months after operation
**Informed consent**	X								
**Collect demographic data**	X								
**Collect medical history**	X								
**Physical examination**	X	X	X	X	X	X	X	X	X
**Routine blood examination**	X	X	X	X	X	X	X	X	X
**Blood biochemical examination**	X	X	X	X	X	X	X	X	X
**Routine urine test**	X		X	X	X	X	X	X	X
**Brain CT scan**	X	X	X	X	X	X	X	X	X
**Brain MRI**	X					X	X	X	X
**CTA/MRA/MRV/DSA (choose 1 or 2 items)**	X								
**HIV, HBV, HCV screening**	X								
**Graeb score**	X	X	X	X	X	X			
**Glasgow Coma Scale**	X	X	X	X	X	X			
**Inclusion/exclusion criteria**	X								
**Randomization**	X								
**Survival rate at 12 months postoperatively**									X
**Modified Rankin Scale**		X	X	X	X	X	X	X	X

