## Abbreviations

IVH: Intraventricular hemorrhage
ICH: Intracranial hemorrhage
EVD: External ventricular drainage
STICH: Surgical Trial in Intracerebral Haemorrhage
AHA/ASA: American Heart Association/American Stroke Association
rtPA: Recombinant tissue-type plasminogen activator
CLEAR: Clot Lysis: Evaluating Accelerated Resolution of Intraventricular Hemorrhage
CTA/MRA/MRV/DSA: Computed tomography angiography/magnetic resonance angiography/magnetic resonance venogram/digital subtraction angiography
SPIRIT: The Standard Protocol Items: Recommendations for Interventional Trials
RAT: Randomization Allocation Tool
CT: Computed tomography
OS: Overall survival
CI: Confidence interval

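### The vascular exclusion can be cleared by a venogram alone, which is not a test for the aneurysm it names first; the permitted examinations and the named diseases should be reconciled

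*Protocol article*

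**What the plan says.** In the protocol article, the Exclusion criteria rule out "Cerebrovascular diseases detected by CTA/MRA/MRV/DSA examinations (choosing 1 or 2 examinations), such as aneurysm and cerebrovascular malformation". The screening column of Table 1 (Outcome measures) carries the same choice: "CTA/MRA/MRV/DSA (choose 1 or 2 items)". The Abbreviations section expands the four as "Computed tomography angiography/magnetic resonance angiography/magnetic resonance venogram/digital subtraction angiography". Three are angiographic studies and the third in the list is a venogram.

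Under Randomization, allocation follows "If the subject is qualified for the trial and signs the informed consent form". Urokinase is then routine in both arms. The Endoscopic group section says "After 6 h postoperatively, we will administer 20,000 U urokinase with 5 ml saline every 8 h through the catheter", and the EVD group section says "After at least 6 h postoperatively, we will administer 20,000 U urokinase with 5 ml saline every 8 h".

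**The concern.** The criterion works through detection: a patient is excluded only if the chosen examination finds the disease. All four examinations are listed as equivalent and one is enough. If the one chosen is not a test for the lesion, the patient passes. Because the site has done what the text asks, this would not even count as a protocol deviation, and monitoring against the protocol would not pick it up.

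Two things are at stake. The first is safety: the sponsor has judged patients with aneurysm unsuitable, yet the wording can admit one to a trial that gives a fibrinolytic in both arms. The second is consistency: four centres choosing different examinations would apply one criterion with different ability to detect what it names.

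**Working it through.** The protocol states no figure on this point, so the check is mainly a reading of the text.

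**1. What the rule permits.** One examination suffices, so there are four single-examination choices: CTA, MRA, MRV and DSA. By the article's own definitions, one of the four (MRV) is a vein study. The criterion and Table 1 agree, so this is the rule as intended and not a slip in one place.

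**2. Whether MRV tests for what is named.** The criterion names aneurysm first, then cerebrovascular malformation, as examples of a wider class. That a venogram is not a test for aneurysm follows from what the examination is; the article does not say it. For malformation and other cerebrovascular disease the position is less clear, and MRV may have a proper place on the list. The point is firm for aneurysm only.

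**3. Whether anything else closes the gap.**
- Inclusion and exclusion criteria: CT is used for the site and extent of haemorrhage and for tumour.
- Table 1: brain MRI is scheduled at screening, but no criterion uses it.
- Setting: the expert panel judges surgical technique.
- Randomization: eligibility and consent are the only conditions; no further vascular check is stated.
- EVD group: the first scan after surgery has another purpose, "Postoperative CT will be done immediately to confirm the positioning of the soft catheter and stability of the hematoma". In the endoscopic arm it assesses residual hematoma. Later scans in both arms look at hematoma and CSF circulation.

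None of these requires a study able to show an aneurysm before randomisation or before urokinase.

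**4. Timing.** The text under Outcome measures lists CTA/MRA/MRV/DSA among the assessments completed during the postoperative stay, whereas Table 1 marks it at screening only. An exclusion has to be settled before randomisation, so these two places also need reconciling.

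**5. Scale, on assumptions only.** Let u be the share of patients cleared by MRV alone and p the share of otherwise eligible patients with a lesion that MRV would miss. The documents give neither. The expected number enrolled against the criterion's intent is 956 × u × p.
- u = 0: 0 patients.
- u = 10%, p = 2%: 956 × 0.10 × 0.02 = 1.9.
- u = 10%, p = 10%: 956 × 0.10 × 0.10 = 9.6.

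The protocol assumes 30% mortality at one year, so expected deaths are 956 × 0.30 = 287, or 956 × 0.95 × 0.30 = 272 after the 5% dropout allowance. If all 9.6 patients in the highest case died, they would make up 9.6/287 = 3.3% to 9.6/272 = 3.5% of deaths. These figures show scale under assumed inputs and are not estimates.

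**The case against.** The strongest reply is that the gap is hypothetical. Nothing in the article says that any centre will use MRV alone. Under Recruitment and consent, screening is in the hands of experienced neurosurgeons, and the criterion tells them in the same sentence what they are looking for. The wording can also be read as letting MRV accompany an angiographic study when venous disease is suspected. The article is a condensed document, and a fuller protocol may hold imaging instructions.

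Much of this stands, and it is why the point is graded low. It does not remove the point. Good judgement at the sites is not a safeguard written into the rule, and the article is not silent on modality: it states a free choice of one or two from four.

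A reader might infer that missed lesions threaten the non-inferiority result, since deaths unrelated to the procedure could pull the hazard ratio towards 1. The documents do not support giving this weight. The examination is scheduled before allocation, randomisation should balance missed lesions between arms, both arms receive urokinase, and even the highest assumed case involves only 3 to 4% of deaths. A reader might also infer that MRV misses every malformation, or that a definite number of ineligible patients will be enrolled. The first goes beyond what the criterion says, and the second rests on two assumed percentages, one of which may be zero.

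**Conclusion.** The point holds in a limited form. As written, the Exclusion criteria and Table 1 let a venogram alone clear a criterion that names aneurysm first, and such a patient would be formally eligible, randomised and given urokinase in either arm. This rests on the article's own definition of MRV and on the general understanding that a venogram is not a test for aneurysm.

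The size is unknown from the documents and probably small. The gap does not by itself bias the randomised comparison. It is a low-frequency matter of participant safety and consistent eligibility, worth correcting because correction is cheap. To treat it as a serious flaw in the trial would overstate what the text shows.

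**What to change.** Reconcile the permitted examinations in the Exclusion criteria and in Table 1 with the diseases the criterion names. The wording should ensure that the examination chosen before randomisation can detect those diseases, and that MRV alone cannot clear the aneurysm exclusion. Which modality to require is for the sponsor to decide. In the same edit, align the Outcome measures text with Table 1, so that it is clear the vascular examination is completed at screening.

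The cost is a short amendment using examinations already on the list. Sites that already choose a suitable study are unaffected. Any site that would have used MRV alone changes modality, and there may be a few more screen failures.
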